### Screening

Potentially eligible patients [(NRS ≥3/10) or clinical diagnosis of chronic dry mouth] will be identified and screened by research staff. The purpose and requirements of the trial will be fully explained and consent sought.

### Trial medication

a) *Active pilocarpine*

Active pilocarpine hydrochloride 4% (40 mg/ml) in citrus solution; 3 drops orally, three times per day (6 mg per dose) with meals, or identical placebo 3 drops three times daily, will be provided in identical opaque bottles and delivered with a mouth dropper. The dose was chosen based on previous studies [15] and a previous report that pilocarpine (15-30 mg/day) improves symptoms in about 50% of patients, compared 25% of patients taking placebo [20]. Placebo and treatment will have identical taste and color, the strong taste of pilocarpine being masked by citrus. The patients will administer the drops themselves unless assistance is required by a clinical nurse.

Trial packs of bottles will be pre-packed by a pharmacy to allow commencement of the trial as soon as the patient is recruited. The drops are stable for one month. The bottles will be labeled with a randomisation number to keep allocation blinded. Single cycle, 6 day packs will be prepared, with random allocation of the order of the medicines determined by computer, individually numbered and allocated to patients consecutively. The Discipline of General Practice at UQ will run the trial centrally and provide randomised medications and diaries by post to the trial sites for dispensing to patients.

b) *Concomitant therapy*

Regular medications will be continued as required for other conditions. Patients who are prescribed new medicines or increased doses of prior medicines that are likely to affect their xerostomia during a cycle will be withdrawn temporarily from the trial, and data from that cycle discarded. The trial can recommence when effects of the change have been stabilised for at least 1 week.

*Compliance* with the study will be measured by bottle weights and completion rates of the diaries at 18 days and will be encouraged by regular telephone calls from the project officer.

### Primary and secondary endpoints

#### Primary outcome

Symptomatic improvement will be measured by NRS score for average dry mouth (answer to the question – how dry was your mouth on average over the last 24 hours?). A clinically significant response to pilocarpine will be defined as a ≥2 point improvement in xerostomia NRS score compared to placebo. This is in view of previous work, where a 20% (2 cm) improvement or more against the baseline score was considered to be a positive improvement [21,22]. NRS data will be collected on days 2 and 3 of each cycle pair to allow wash-out during day 1.

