### Aggregated n-of-1 trial design

This will be an n-of-1 trial with 3 pairs (cycles) of treatment periods comparing active drug to placebo. As pilocarpine has a short half life (0.76 hours for 5 mg tabs), the clinical effect is rapidly evident. Therefore, an appropriate duration of each treatment period is 3 days (thus each treatment pair (or cycle) is 6 days), making a total of 18 days for patients who complete the full trial. The order of drugs in each cycle will be determined by random allocation, blinded to both clinician and patient. Patients who do not complete the full trial will still contribute completed cycles to the final analysis. To produce a population estimate of a treatment effect, the results of all patient cycles will be aggregated [18].

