EORTC-QLQC15-PAL core items	x				x
Adverse Event Reporting^1^	x	x	x	x	x
Xerostomia NRS		x			
Xerostomia inventory		x			
Number of breakthrough salivary substitute uses		x			
Dysphagia		x			
Dysgeusia		x			
Changes in xerostomia related medications		x			
OHIP			x		
PGIC			x		

^1^Telephone assessment conducted by research officer.

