#### Data analysis

Data preparation and descriptive reporting will follow that recommended by the CONSORT statement [25].

For each cycle, data from day 1 will be discarded to allow for a wash-out period, and data from days 2 and 3 data will be analysed. All patients with at least one completed treatment cycle will be included in analyses. An effect size will then be calculated between active medication cycles and placebo, thus providing a population measure of effect commensurate with an RCT.

Both individual and population treatment differences will be estimated using hierarchical Bayesian methods and employing noninformative priors using the methods described in Zucker et al. [33], and Schluter and Ware [34]. The likelihood distributions for each model will be assessed for violations and data transformations undertaken, where necessary. Conventional burn-in periods, model convergence and stability diagnostics, and residual checks will be employed [35]. WinBUGS [35] will be used for the Bayesian analysis.

To describe participants’ overall response, three types of Bayesian results will be presented: (i) the mean of the posterior distribution of the mean difference between placebo and stimulant scores, which gives the best estimate of the overall effect size difference between treatments; (ii) the associated 95% credible region, which give intervals of uncertainty (in this case the 2.5 and 97.5 percentile) of the posterior distributions used in (i); and (iii) the posterior probability of the mean difference that stimulant scores were better than placebo scores, which describes the likelihood that the patients will favour the active treatment in future cycles [34]. A patient will be defined to be a ‘responder’ when these estimated values exceed predefined threshold values [34].

Important confounding variables, such as anti-cholinergic load and cause of xerostomia (eg prior radiotherapy), will in included in adjusted analyses and report treatment effects (or success differences) over the various variable stratifications and combinations, following the method advocated by Zucker and colleagues [33].

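### The wash-out and analysis window is attached to the 6-day cycle instead of the 3-day treatment period, so the second period of each cycle has no stated analysis days and no stated wash-out day

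*Protocol article*

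**What the plan says.** The section Aggregated n-of-1 trial design fixes the vocabulary. The study is an "n-of-1 trial with 3 pairs (cycles) of treatment periods comparing active drug to placebo", with "duration of each treatment period is 3 days (thus each treatment pair (or cycle) is 6 days), making a total of 18 days". It adds that "The order of drugs in each cycle will be determined by random allocation", so each cycle holds one active and one placebo period. The Trial medication section (6-day single-cycle packs) and Table 1 (a column for the end of the 6-day cycle) use the word in the same sense.

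Two places define the data for the primary outcome:

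- Primary outcome: "NRS data will be collected on days 2 and 3 of each cycle pair to allow wash-out during day 1".
- Data analysis: "For each cycle, data from day 1 will be discarded to allow for a wash-out period", with days 2 and 3 then analysed.

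The Data analysis section goes on: "An effect size will then be calculated between active medication cycles and placebo". Table 1 lists "Xerostomia NRS" under the daily column.

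**The concern.** The window fits a 3-day block but is attached to a unit that the article defines as 6 days long. Days 4 to 6 of a cycle, the whole second treatment, fall under neither the discard rule nor the analysis rule.

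That leaves two readings. Either the second period is not used, and the within-cycle comparison on which the design rests is lost. Or it is used, and the plan does not say whether day 4, when the patient changes treatment within the cycle, is dropped. The second reading leaves a choice about primary-outcome data to be made later.

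Two related slips add to the uncertainty. The Data analysis section speaks of cycles of active medication, although every cycle contains both treatments. The Primary outcome section has the NRS collected on days 2 and 3, while Table 1 has it daily.

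**Working it through.** **1. Calendar.** From Aggregated n-of-1 trial design: period = 3 days, 2 periods per cycle, 3 cycles. 2 × 3 = 6 days per cycle and 3 × 6 = 18 days in total. Both stated figures reproduce.

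| Cycle day | Period | Rule as written | Rule read per 3-day period |
|---|---|---|---|
| 1 | first | discard | discard |
| 2, 3 | first | analyse | analyse |
| 4 | second | not mentioned | discard |
| 5, 6 | second | not mentioned | analyse |

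**2. Expected data.** Sample size calculations expects 31 patients to complete three cycles, 4 to complete two, 7 to complete one, and 28 to complete none of the 70. Analysable patients: 31 + 4 + 7 = 42. Completed cycles: 31 × 3 + 4 × 2 + 7 = 108, or 216 periods.

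- Per period: 4 scores per cycle, 108 × 4 = 432 daily scores, half on each treatment.
- As written: 2 scores per cycle, 108 × 2 = 216, from first periods only (108 of 216 periods).

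**3. Patients with only one treatment observed, literal rule.** Assume the first treatment is allocated 1:1, independently in each cycle. All first periods carry the same treatment with probability 1 (one cycle), 0.5 (two cycles) or 0.25 (three cycles). Expected number: 7 × 1 + 4 × 0.5 + 31 × 0.25 = 16.75 of 42.

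**4. Within-patient information.** For a patient with nA active and nP placebo periods, take nA·nP/(nA + nP).

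- Both periods: 31 × 1.5 + 4 × 1 + 7 × 0.5 = 46.5 + 4 + 3.5 = 54.
- First periods only: 31 × (0.75 × 2/3) + 4 × (0.5 × 1/2) + 0 = 15.5 + 1 = 16.5.
- Ratio 16.5/54 = 0.306. Standard error multiplier √(1/0.306) = 1.81.

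**5. Random-intercept model.** This also uses differences between patients. It takes one mean per analysed period, with the same 108 cycles. The first-period-only results are averaged over 500 random sets of treatment orders. With both periods, SE = √(2·s_w²/108). Total variance is 2.975² = 8.851. Two values of s_w² were used, because an ICC of 0.3 gives 0.7 × 8.851 = 6.195 while the article states 4.752.

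| s_w² | s_b² | SE, both periods | SE, first period only | Ratio |
|---|---|---|---|---|
| 6.195 | 2.655 | 0.339 | 0.537 | 1.58 |
| 4.752 | 4.099 | 0.297 | 0.490 | 1.65 |

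**The case against.** The strongest reply is that the meaning is plain. The sentence "An effect size will then be calculated between active medication cycles and placebo" uses *cycle* for a block on a single treatment, which is 3 days long. In that sense, dropping day 1 and keeping days 2 and 3 covers the block exactly. A rule that left days 4 to 6 of a 6-day unit without instruction would be odd. The paired design, the individual treatment differences and the repeated-measures simulation all presuppose data on both treatments. This stands as evidence of intent. It does not make the text correct: the rule is misstated in both places that set the primary dataset, and nowhere is it stated per treatment period.

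Four stronger readings are tempting, and the document does not support them.

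- *The trial will drop the second period.* Nothing shows this. Table 1 has the NRS daily, so the scores would exist.
- *The second period is lost and carry-over also contaminates the result.* These are alternatives. Under the literal rule day 4 is not analysed either. The missing wash-out matters only if the second period is used.
- *The planned analysis would lose precision by a factor of 1.8.* That figure counts within-patient information only. The planned model is hierarchical and can also use between-patient information, which gives roughly 1.6. In the same simple model a 2-point difference would still have about 96% to 98% power (two-sided 5%) under the literal rule. That model does not reproduce the stated 80% at n = 70, so it serves only as a check of scale.
- *NRS data are missing on the other days.* Discarding day-1 data implies that they are collected, so the Primary outcome wording is probably loose for the days used.

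The time of day at which the 24-hour recall score is completed is a diary detail that an article may leave to the full protocol. It is no part of this point.

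**Conclusion.** The point holds as an error in a stated rule, with an intent that is easy to infer. On the article's own definition, "each treatment pair (or cycle) is 6 days", the rule selects data from the first period alone. Corrected by inference to include the second period, it still names no wash-out for day 4.

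Followed literally, it would leave no active-placebo pair in any cycle, about 17 of 42 analysable patients with one treatment only, and a standard error about 1.6 times the intended one (1.8 times on within-patient information alone). These sizes rest on the article's expected completion, 1:1 random order in each cycle, one mean per period, and a random intercept without variation in treatment effect between patients. They describe the literal text and are not a forecast of what the trial would do.

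It deserves correction because this rule selects the primary-outcome data, and readers should not have to repair it by inference.

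**What to change.** - In Primary outcome and in the wash-out sentence of Data analysis, replace the cycle (or cycle pair) by each 3-day treatment period. Spell it out: discard cycle days 1 and 4, analyse days 2-3 and 5-6.
- In the effect-size sentence of Data analysis, refer to active treatment periods instead of cycles.
- In Primary outcome, say that the NRS is collected daily, as in Table 1, and that the named days are those analysed.
- Confine the replacement to these sentences. The rule that patients need at least one completed cycle can keep the 6-day meaning, which is how the sample-size section counts completion.

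The cost is wording only. Table 1 already has the NRS recorded daily, so no data collection is added.

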#### Secondary outcomes

1. Mean xerostomia inventory score [23];

2. Oral health related quality of life;

3. Adverse events (according to NCI Common Terminology for Adverse Events [24]);

4. Dysphagia (difficulty swallowing);

5. Dysgeusia (distortion of taste);

6. Global impression of change.

The trial will be reported according to the Consort statement [25], and analysis will be on an intention-to-treat basis.

### Patient assessment

1. *Outcome Measures*

The schedule of assessments is presented in Table 1. The outcome measures assess different aspects of the trial as follows:

(a) *Response to pilocarpine*:

(i) Numerical rating scale (NRS) for xerostomia. The NRS consists of a range of numbers, with the smaller numbers indicating less dry mouth. An 11-point NRS rates symptom intensity corresponding to an integer number between 0 and 10. People rate their dry mouth by marking a number on a paper that lists the numbers horizontally in ascending order. The NRS has well-established psychometric properties; being valid, reliable, and sensitive to change. It is nonintrusive, easy to administer and score, and suitable for repeated use [26]. Although no studies were found on the psychometric properties of NRS in xerostomia, NRS are commonly used in studies of this condition. Severity of xerostomia will be measured using a 0-10 cm NRS ranging from 0 = no dry mouth to 10 = worst possible dry mouth. At each assessment point, patients will be asked to score their current, worst, best and average dry mouth score over the preceding 24 hours. Dysphagia and dysgeusia (a distortion of the sense of taste) scores will also be recorded in a daily diary using a 0-10mm NRS.

(i) The xerostomia inventory (XI) [23], a valid and reliable scale for measuring xerostomia symptoms, will also be used as a secondary measure.

(a) *Performance status*:

Australian Karnofsky Performance Scale (AKPS) [27]. This scale assesses functional performance and is a validated modification of the gold-standard Karnofsky Performance Scale, altered to apply to both community and hospital patients. It has high test-retest reliability, high predictability of survival time, and sensitivity to change towards the end of life.

(a) *Presence of side-effects*:

Any toxicity will be rated using the National Cancer Institute Common Terminology Criteria for Adverse Events (NCI CTC AE) v3.0 [24]. The trial will be overseen by an independent data safety monitoring committee.

(a) *Quality of life (QOL) indicators:*

(i) EORTC-QLQC15-PAL core items [28], is a general cancer QOL questionnaire suited to a palliative sample as it yields data on overall QOL, physical, emotional and social functioning and other symptoms, has been extensively validated, has reference data available and uses standardised scoring procedures, with evidence concerning interpretation of scores.

(i) Oral health related quality of life will be measured by Oral Health Impact Profile (OHIP) [29], a short 14 item questionnaire that has been validated in a population with xerostomia, although not in cancer or PC.

(a) *Patient Global Impression of Change (PGIC)*:

Is a standardised, validated questionnaire that addresses change in activity limitation, emotions, symptoms and overall quality of life [30].

2. *Timing and content of assessments*

3. *Individual patient reports*

At the end of the trial, the order of medications will be unmasked, and compared with the patient’s observations. Repeated results in the same direction favouring the treatment will be reported in terms of a probability that the observed result is true. The clinical importance of the result will be described by comparing it to a predetermined clinically important change. A clinically significant response to pilocarpine or placebo will be defined as a ≥2 point improvement in xerostomia NRS score compared to baseline, in view of previous work, where a 20% (2 cm) improvement or more against the baseline NRS score was considered to be a positive improvement [21,22]. A report on the patient’s response to pilocarpine will be forwarded to the patient’s doctor so a decision on further treatment can be made.

Palliative care clinicians who recruit participants will most likely also receive the post-treatment report. This potentially may unblind the clinician during the course of the trial in relation to the possible effectiveness of pilocarpine, and particular characteristics of responders. Ideally the clinician recruiting to the study will be a different to the one receiving the results and treating the patient. Collecting data from patients independent of clinicians minimises observer bias.

4. *Withdrawals*

Patients who discontinue the study for whatever reason will be able to resume if their condition can be re-stabilised for at least 1 week. Patients who cannot resume the trial will have their completed cycle results added to the trial dataset for later calculation of the population effect of pilocarpine. If a patient’s withdrawal from the study could be attributed to the intervention, their data will contribute to the analysis under intention to treat principles.

**Table 1 T1:** Schedule of assessments

**Measure**	**Baseline**	**Daily**	**Every 3 days**	**End of 6 day cycle**	**End of trial**
Demographics	x				
Vital Signs	x				
Routine blood test	x				
AKPS	x				x^1^
EORTC-QLQC15-PAL core items	x				x
Adverse Event Reporting^1^	x	x	x	x	x
Xerostomia NRS		x			
Xerostomia inventory		x			
Number of breakthrough salivary substitute uses		x			
Dysphagia		x			
Dysgeusia		x			
Changes in xerostomia related medications		x			
OHIP			x		
PGIC			x		

^1^Telephone assessment conducted by research officer.

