### Participants

a) Inclusion criteria:

1. Patients aged ≥18 years with malignant disease;

1. a clinical diagnosis of chronic dry mouth that has been present for at least 2 weeks with no likelihood of resolution during the trial period

1. a numerical rating scale (NRS) score of ≥3 on a 11-point xerostomia scale;

1. no known allergy or sensitivity to pilocarpine;

1. ability to give fully informed written consent and complete all trial requirements.

b) Exclusion criteria:

1. no plan to change any medication with the potential to cause dry mouth within the trial period. (Patients already on pilocarpine are eligible but must stop this 1 week before trial commencement);

1. no intervention e.g. radiotherapy, chemotherapy, surgery that might alter dry mouth symptoms during the 2 weeks prior to the study period or plans to undergo such therapy during the study period;

1. ocular problems contraindicating the use of parasympathetic agents (eg irido-cyclitis, increased intra-ocular pressure);

1. other comorbidity where there is a risk of worsening co-existing medical problems during the trial period and/or active treatment is contemplated (e.g. severe or uncontrolled asthma or pulmonary disease, uncontrolled hypo-or hypertension, hyperthyroidism, uncontrolled seizures or cardiac arrythmias, (especially bradycardias) and Parkinson's disease);

1. a poor understanding of written or spoken English that would preclude completion of all trial requirements;

1. an active oral infection (e.g. candidiasis, herpetic infections, mucositis, mouth ulcers).

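### Clinically significant response to pilocarpine is measured against placebo in the primary outcome but against baseline in the individual patient reports, and the baseline rule can be met without any drug effect

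*Protocol article*

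**What the plan says.** Under Primary outcome, the protocol article states: "A clinically significant response to pilocarpine will be defined as a ≥2 point improvement in xerostomia NRS score compared to placebo". It supports the threshold with earlier work "where a 20% (2 cm) improvement or more against the baseline score was considered to be a positive improvement".

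Under Patient assessment, item 3 (Individual patient reports), it states: "A clinically significant response to pilocarpine or placebo will be defined as a ≥2 point improvement in xerostomia NRS score compared to baseline". The threshold and the two citations are the same as before. The report goes to the patient's "doctor so a decision on further treatment can be made". The same paragraph provides for unmasking the order of medications and adds: "Repeated results in the same direction favouring the treatment will be reported in terms of a probability that the observed result is true".

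Under Data analysis, posterior summaries of the difference between placebo and active scores are to be presented, and a patient is called a responder "when these estimated values exceed predefined threshold values", with a method reference.

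Entry requires "a numerical rating scale (NRS) score of ≥3 on a 11-point xerostomia scale". In Table 1 the row "Xerostomia NRS" is marked under Daily only.

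**The concern.** One term has two meanings in the current text. A patient who improves by 3 points on both drops has a clinically significant response to pilocarpine under the individual-report rule and none under the primary-outcome rule.

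The secondary aim is to tell each patient and clinician whether pilocarpine works for that patient. An n-of-1 design does this by comparing the patient's active periods with the same patient's placebo periods. A comparison with baseline does not isolate the drug. Patients enter because their score is high enough, so part of any later fall is regression to the mean, and any placebo response is added to it. At stake is the label of clinical importance in the report that guides treatment after the trial.

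**Working it through.** The article gives no response or misclassification rate, so there is no figure to reproduce. The size below is illustrative.

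**Inputs from the article.** Baseline SD 2.975, ICC 0.3 and within-patient variance 4.752 (Sample size calculations); 3 cycles; entry at NRS of at least 3; threshold 2 points. SD and ICC together imply a different within-patient variance from the printed one: 0.7 × 2.975² = 0.7 × 8.851 = 6.195. Both values were used. The between-patient variance is the remainder: 8.851 − 4.752 = 4.099, or 8.851 − 6.195 = 2.655 (rounded down).

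**Assumptions not in the article.** True drug effect zero; population mean 3.25 (the planning value), 5 or 6; baseline is one reading; each period contributes one value.

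**Closed form, without entry selection, 3 cycles.** Write s² for the within-patient variance.

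- Baseline minus mean of 3 active periods: variance s²(1 + 1/3) = 4s²/3. For 4.752 the SD is √6.336 = 2.517 and P(≥2) = 1 − Φ(2/2.517) = 21%. For 6.195 the SD is √8.260 = 2.874 and P = 24%.
- Mean placebo minus mean active: variance s²(1/3 + 1/3) = 2s²/3. For 4.752 the SD is √3.168 = 1.780 and P = 13%. For 6.195 the SD is √4.130 = 2.032 and P = 16%.

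**Simulation with entry at NRS of at least 3.** Scores are integers limited to 0-10, with no drug effect and no placebo effect. Share of patients meeting the baseline rule on pilocarpine:

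| Within-patient variance | Mean 3.25 | Mean 5 | Mean 6 |
|---|---|---|---|
| 4.752 | 34% | 27-28% | 24-25% |
| 6.195 | 39% | 32% | 28% |

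Across these six scenarios:

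| Classification | Share of patients |
|---|---|
| Baseline rule met on pilocarpine | 24-39% |
| of which met on placebo as well | 15-26% |
| of which met on pilocarpine only | 10-13% |
| Placebo rule met (placebo minus pilocarpine ≥2) | 13-17% |

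**Sensitivity.** If days 2 and 3 are treated as independent readings and averaged, and a lower between-patient variance (2.037) is also allowed, the baseline rule gives 22-36% and the placebo rule 5-7%. With an assumed 1-point placebo effect, the baseline rule rises to 37-55% over all settings, while the placebo rule stays within 4-16%. The baseline rule gave the higher rate in every scenario run.

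**The case against.** The strongest reply is that the individual-report paragraph must be read whole. Its baseline rule applies to pilocarpine and placebo alike, and the paragraph also reports a probability for repeated results that favour treatment. The patient who improves by 3 points on both drops would be shown as responding to both, with no repeated advantage for pilocarpine. A reader might infer from the 24-39% that the reports would present that share of unaffected patients as helped by the drug. The article does not support this: only 10-13% meet the baseline rule on pilocarpine and not on placebo, which is no worse than the 13-17% under the placebo rule. This part of the reply stands. It does not remove the contradiction. The probability speaks to direction; clinical importance is judged by the baseline rule, and a response to pilocarpine as defined there needs no difference from placebo.

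Four further inferences are tempting and should not be drawn.

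- *Data analysis adds a third conflicting definition.* Its quantities are summaries of the placebo-active difference, consistent with the primary outcome. The threshold values may stand in the analysis plan or the cited method.
- *There is no baseline score.* Eligibility needs an NRS, so one exists. Table 1 lacks a mark, and the article does not name the eligibility score as the baseline; both are minor.
- *Two points is 62% of baseline, so the 20% rationale fails.* That figure is 2/3.25, the mean in the cited study. Under the entry rule the simulated enrolled means are about 5.2 to 6.5, so 2 points is about 31-39%. Both rules already state the threshold as an absolute 2 points.
- *The 25% improvement on placebo quoted under Trial medication confirms the simulated rates.* The article does not say how improvement was defined there.

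**Conclusion.** The point holds as a contradiction between two current definitions, and the baseline rule is wrong as written for a report meant to show individual response to pilocarpine. With no drug effect, 24-39% of patients would meet it on pilocarpine, against 13-17% under the placebo rule. The practical harm is smaller if each report also shows the placebo classification and the directional probability.

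These rates rest on the assumed population means, a single baseline reading, one value per period and completion of all 3 cycles. The direction does not depend on the choices tested.

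The problem is confined to the secondary aim. The population estimate uses the placebo-active difference, the sample size is set for a difference between treatments, and a responder count is not among the listed endpoints. It should be fixed, but it does not threaten the primary result.

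**What to change.** - In Individual patient reports, replace the baseline definition with the one under Primary outcome: the patient's own placebo-minus-pilocarpine difference, at least 2 points.
- In Data analysis, state that the predefined responder thresholds apply to that same difference. The form of the threshold is the trial team's choice. A cut-off on the posterior probability of a difference of at least 2 points is one option, but a demanding one: for a patient whose true benefit is exactly 2 points, that probability centres near 50% even before shrinkage.
- Keep change from baseline as description only, shown for both drops, with the eligibility NRS named as the baseline and marked in Table 1.

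This costs a wording change and no extra data. The downside is that fewer patients will be labelled responders. The change should be made before the first report is sent, because a report already acted on cannot be recalled.
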